### 3.7 Safety Evaluation

This study does not involve safety issue, so safety evaluation is not required. This study will collect adverse events on the treatment of RA.

### 3.8 Subject Protection

This clinical trial should not start until the clinical trial protocol and the informed consent form of the subjects have been submitted and approved by the Ethics Committee of Peking University People's Hospital. If the protocol is revised, only the corresponding revised part and the revised informed consent can be implemented after being reviewed and approved by the ethics committee, and a copy of the approval by the ethics committee of Peking University People's Hospital is required to be provided to the clinical inspector. If the protocol is revised to reduce the obvious risk of the subjects, it can be implemented immediately, but it must be submitted to the relevant departments and the ethics committee for the record as soon as possible.

Subjects can obtain information on RA disease knowledge and free online learning of RA knowledge, and get a free consultation.

The investigators keep the subject's evaluation results confidential. In the study, the identity information of the subjects was de-identified. The patients in the conventional treatment group used initials instead of the real names of the patients. The SSDM group can use the users' name (non-real name) for registration and subsequent login. All data is only used in this study.

### 3.9 Management of Clinical Study

If the protocol is revised, only the corresponding revised part and the revised informed consent can be implemented after being reviewed and approved by the ethics committee, and a copy of the approval by the ethics committee of Peking University People's Hospital is required to be provided to the clinical inspector. If the protocol is revised to reduce the obvious risk of the subjects, it can be implemented immediately, but it must be submitted to the relevant departments and the ethics committee for the record as soon as possible.

If severe safety issues arise during the trial, or major mistakes in the clinical trial protocol were found during the trial, the sponsor or the administrative department should request termination or the trial.

### Protocol Amendment

**Amendment 1 19.04.12** The alert function has been added to the protocol.

In Brief, A red flag was raised upon one or more of the following conditions:

1. Disease activity exacerbation: the DAS28-CRP score increased to and remained at 3.2-5.1 (moderate disease activity, MDA) for 3 months, or increased to  $> 5.1$  (high disease activity, HDA) in patients with remission (REM,  $\text{DAS28-CRP} \leq 2.6$ ) or low disease activity (LDA,  $> 2.6$  but  $\leq 3.2$ ) at baseline;
2. Sustained MDA or worsening HDA: the DAS28-CRP score remained at 3.2-5.1 for 3 months, or increased to  $> 5.1$  in patients with MDA at baseline;
3. HDA status: the DAS28-CRP score remained at  $> 5.1$  for 3 months, decreased to 3.2-5.1 but with subsequent exacerbation (DAS28-CRP increase to  $> 5.1$ ) at any time point or no further reduction by at least 1.2 within 3 months in patients with HDA at baseline.
4. The alert was also triggered upon elevated alanine aminotransferase or aspartate aminotransferase levels above 2-times the upper normal limit or a white blood cell count of  $< 2,000$  or  $> 10,000$  per mL.

**Management of rheumatoid arthritis with a mobile health application: A  
multi-center, pragmatic randomized controlled trial**

**Statistical Analysis Plan**

**Analysis Summary**

**1. Study Title**

Management of rheumatoid arthritis (RA) with a mobile health application: A multi-center, pragmatic randomized controlled trial

**2. Primary Objectives**

The primary outcome was the rate of patients with DAS28-CRP  $\leq 3.2$  at month 6

**3. Secondary Objectives**

- (1) The proportion of patients with moderate-to-good EULAR response rate at month 6
- (2) ACR/EULAR Boolean remission rate at month 6 and month 12
- (3) The change in simplified disease activity index (SDAI) at month 6 and month 12
- (4) The change in clinical disease activity index (CDAI) at month 6 and month 12
- (5) The change in tender joint counts at month 6 and month 12
- (6) The change in swollen joint counts at month 6 and month 12
- (7) The change in Hospital Anxiety and Depression Scale (HADS) at month 6 and month 12
- (8) The change in the 36-Item Short Form Survey (SF-36) at month 6 and month 12
- (9) Flare rate at month 6 and month 12 at month 6 and month 12
- (10) The rate of patients achieving DAS28-CRP-CRP  $\leq 3.2$  at month 12
- (11) The numbers and rates of adverse events, either reported by the rheumatologists or resulting from an alert in the SSDM.

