#### 192 2) Intervention

193 ① SSDM intervention group: Upon the first use of the system, the following information must be  
194 entered with the help of a research staff: full name, sex, date of birth, date of initial diagnosis,  
195 comorbidities, education level, occupation, family income, annual medical expenses and DAS28-CRP  
196 at each research site. Other information that entered included: 1) lab results (e.g., routine blood test,  
197 liver and kidney function, erythrocyte sedimentation rate, CRP), submitted as photographs and  
198 automatically processed to extract key information via Optical Character Recognition technology; 2)  
199 medications, for RA as well as co-morbid conditions; and 3) perceived adverse reactions (a total of 33  
200 types of symptoms).

201 Patients randomized to the SSDM group watch a 15-minute video that described the key features of  
202 SSDM to allow correct use of the app. After learning, the patients will do the self-assessment all by  
203 themselves using SSDM. If there is inconsistency between patient and physician, the physician will  
204 correct it and then the patient will do it again. At last, the use of SSDM by patients and self-assessment

205 of DAS28-CRP were confirmed by physicians.

206 ② Conventional care control group: Patients randomized to the control group will receive  
207 conventional care, and should come back for office visits at month 6 and month 12. The information of  
208 baseline characteristics will also be collected.

209 All the primary and secondary endpoint will be assessed by rheumatologists.

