### 217 2) The Secondary Endpoint

218 ① The rate of DAS28-CRP  $\leq 3.2$  between the two groups at month 12, assessed by rheumatologists.

219 ② The RA flare rate between the two groups at month 6 and 12.

220 ③ The proportion of patients with moderate-to-good EULAR response between the two groups at  
221 month 6 and 12.

222 ④ ACR/EULAR Boolean remission rate between the two groups at month 6 and 12.

223 ⑤ The HADS between the two groups at month 6 and 12.

224 ⑥ The SF-36 between the two groups at month 6 and 12.

225 ⑦ Clinical disease activity index (CDAI) between the two groups at month 6 and 12.

226 ⑧ The numbers of tender joint counts and swollen joint counts between the two groups at month 6 and  
227 12.

⑨ The effect of active intervention by doctors between the two groups at month 6 and 12.

⑩ The number and rate of adverse events, either reported by the rheumatologists or resulting from an alert in the SSDM.

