#### 6.8 Safety Analyses

This study does not involve safety issues, so safety evaluation is not required. The perceived adverse events will be collected. The adverse events were not assessed for both trial arms and were not able to be compared between the two groups.

Adverse events are defined as any general lack of well-being, symptoms of illness, or laboratory parameters outside the normal range.

Serious adverse events are defined as any life-threatening or fatal event.

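### As defined, the adverse event endpoint can mix RA disease activity and abnormalities already present at entry with harm

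*Combined protocol and SAP*

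**What the plan says.** The endpoint appears in the protocol, section 3.3 (5) 2), last item: "The number and rate of adverse events, either reported by the rheumatologists or resulting from an alert in the SSDM". SAP section 3, item (11), repeats it almost word for word: "The numbers and rates of adverse events, either reported by the rheumatologists or resulting from an alert in the SSDM". SAP 6.7 lists the number and rate of adverse events among the secondary endpoints without naming any source.

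Amendment 1 defines the alert: "A red flag was raised upon one or more of the following conditions". Four conditions follow. The first three open with "Disease activity exacerbation: the DAS28-CRP score increased to and remained at 3.2-5.1", "Sustained MDA or worsening HDA: the DAS28-CRP score remained at 3.2-5.1 for 3 months" and "HDA status: the DAS28-CRP score remained at" (above 5.1). The fourth concerns liver enzymes and white cell count.

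SAP 6.8 gives the definition: "Adverse events are defined as any general lack of well-being, symptoms of illness, or laboratory parameters outside the normal range". The same section says that perceived adverse events will be collected, and that adverse events were not assessed in both arms and cannot be compared between them.

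Protocol section 3.3 (2) 2) lists, among the information entered in the app by the SSDM group, "perceived adverse reactions (a total of 33" types of symptoms).

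**The concern.** An adverse event rate is read as a measure of harm. Here two stated rules let something else in. One source of events is an alert that is raised largely on the efficacy variable. The definition also asks for no change from the patient's state at entry, although every participant has RA and many will enter with joint symptoms or a raised CRP.

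If disease activity is counted, a fall in DAS28-CRP lowers the adverse event rate with no change in drug harm, and a patient who simply stays in moderate activity can add to it. Worsening already has its own secondary endpoint, the flare rate (SAP section 3, item 9), so the same episode could be reported under both. In addition, two analysts following the text could disagree on whether a symptom entered only in the app belongs in the count.

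**Working it through.** The documents give no expected rate, sample size or power for this endpoint, so there is no planned figure to reproduce. The check is a comparison of the rules, followed by what can be said about size.

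**Step 1. What raises an alert (Amendment 1).**

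| Condition | Based on | RA activity? |
|---|---|---|
| 1 | DAS28-CRP rising, from remission or low activity at baseline | yes |
| 2 | DAS28-CRP staying moderate or rising to high, from moderate at baseline | yes |
| 3 | DAS28-CRP staying high, worsening again, or not falling enough, from high at baseline | yes |
| 4 | ALT or AST, or white cell count | no |

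Three of four are RA activity. Under condition 2, a patient who enters with moderate activity and stays there for 3 months raises the flag without any change of state.

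**Step 2. How an alert becomes an event.** No section gives a rule. Two readings are open:

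- The alert is itself the event. Conditions 1 to 3 then enter the count directly.
- The alert is the route by which an event is found. The event must then meet the SAP 6.8 definition. A patient flagged for activity will ordinarily have joint symptoms, and that definition excludes neither RA symptoms nor symptoms present at entry. Activity can still enter.

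**Step 3. The definition against the disease measure.** Appendix 1 builds DAS28-CRP from tender joints, swollen joints, CRP and a general health scale. Tender joints are a symptom of illness, a raised CRP is a laboratory value outside the normal range, and poor general health is close to the first limb of the definition. Without a baseline comparison, ordinary active RA on the day of entry meets SAP 6.8.

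**Step 4. Perceived reactions.** The endpoint names two sources: rheumatologist reports and alerts. The 33 symptom types are neither a named source nor an alert condition. SAP 6.8 nevertheless collects perceived events and defines adverse events to include symptoms. The sections do not settle whether the app entries count.

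**Step 5. Size.**

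- Earlier SSDM cohort (protocol 3.4): 122 relapsed and 317 never reached target. 122 + 317 = 439, and 439/1232 = 35.6% were not in remission or low activity after 6 months.
- Design assumption (SAP 6.3): 52% of the SSDM arm at or below 3.2, so 1 - 0.52 = 48% above it. With 2204/2 = 1102 per arm, 0.48 x 1102 = 529 patients.

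These are patients above target at one time point, not alerts. To show how little the documents fix, let *a* be the share of SSDM patients with an activity alert counted as an event, and *b* the share with an event from a laboratory alert or rheumatologist report. Both are assumed, with no overlap. The activity share is a/(a + b):

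- a = 5%, b = 40%: 0.05/0.45 = 11%
- a = 25%, b = 20%: 0.25/0.45 = 56%
- a = 48%, b = 2%: 0.48/0.50 = 96%

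The range is too wide to say which component dominates.

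**The case against.** The strongest reply is that the counted unit is an adverse event, not an alert. Amendment 1 labels conditions 1 to 3 as disease activity and never calls a red flag an adverse event. Protocol 3.7 says that the events to be collected are those on the treatment of RA, which points to treatment harm. SAP 6.8 collects perceived events, so the app symptoms are not plainly left out. The arms are not to be compared, so no between-arm safety claim rests on the rate, and the statement that SSDM reduces adverse events is background from preliminary work.

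Much of this stands. A reader might infer that every alert is counted, that the 33 symptoms are excluded, and that the rate therefore measures treatment failure instead of harm in a third to a half of the SSDM arm. The documents do not support that. Coming from an alert need not mean being one. The fault with the symptoms is an unresolved conflict, not a clear omission. Three of four is a count of rules, not a share of events. Being above 3.2 at month 6 does not show that an alert was raised, and a patient at target then may have alerted earlier. Nor is there a contradiction in liver enzymes between one and two times the upper limit meeting the SAP 6.8 definition without raising an alert: one rule defines an event, the other sets a notification threshold, and a rheumatologist can still report the value.

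What the reply does not answer is that no section excludes activity alerts, none asks for change from baseline, and none says whether app-entered symptoms count.

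**Conclusion.** The concern holds as a fault of definition. The stated rules let RA activity and abnormalities present at entry into the adverse event rate, on either reading of the alert source, and they leave the status of the perceived reactions unsettled. The rate can mix disease activity with harm; whether it mostly does so cannot be determined.

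Confidence is high on the wording and low on the size. The 36% and 48% figures mark how many patients could be exposed, and turning them into event rates would need alert data that the documents do not contain. The consequence is limited because the endpoint is secondary and, by SAP 6.8, descriptive. It still needs a usable definition, first within the SSDM arm and then, after month 6, for control patients who move to the app and start to generate alerts.

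**What to change.** In SAP section 3 item (11), SAP 6.7 and 6.8, and protocol section 3.3 (5) 2):

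1. Count as adverse events only symptoms, signs or laboratory abnormalities that are new or worse than at baseline.
2. Tabulate alerts under conditions 1 to 3 separately as disease-activity alerts, not as adverse events.
3. Name the perceived-reaction entries as a source beside rheumatologist reports and laboratory alerts, and state when they are recorded, so that the endpoint wording and SAP 6.8 agree.
4. Present the number and rate descriptively, for patients while they use SSDM, with no comparison between arms.

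The cost is wording and tabulation, provided that the app holds dated entries, including one at baseline. Each event must be checked against the baseline entry, and the app symptom source exists only for SSDM users, so the rate cannot be extended to control patients before they switch. The change concerns what is counted; it leaves the alert conditions and patient care as they are.

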**4. Patient Population**

All patients diagnosed with RA who are treated at Peking University People's Hospital and other clinical trial centers.

**4.1 Inclusion criteria:**

- (1) Diagnosis of RA by investigators according to the 2010 American College of Rheumatology (ACR)/European League Against Rheumatism (EULAR) criteria
- (2)  $\geq 18$  years old
- (3) Have a smartphone
- (4) Able to evaluate disease activity by themselves

**4.2 Exclusion criteria**

- (1) Not able to read and use smartphone
- (2) Not able to perform the joint examination by themselves
- (3) Patients with cognitive impairment or mental condition which make them unable to comply with the requirements of self-management
- (4) Hand deformations or any other conditions (e.g., Parkinson's disease and late-stage Alzheimer's disease) that affect data input

(5) Do not want to accept the treatment of RA or do not plan on receiving follow-up care at the research centers

(6) Already a user of SSDM

### 4.3 Withdrawal criteria

Patients who request to withdraw from the clinical trial.

## 5. Study Design

[figure not shown]

## 6. Statistical Procedures

### 6.1 Introduction

Mobile health applications (apps) have been shown to be effective in the management of chronic diseases with simple treatment target (e.g., hypertension). The potential clinical value of mobile health apps in RA has not been well studied.

The objective of this study is to investigate whether assessing patient reported outcomes using mobile health apps could result in improving outcomes in RA patients. This is a multicenter, randomized controlled trial in 22 tertiary hospitals across China. Eligible participants are adult RA patients with a smartphone. RA patients, regardless of baseline disease activity, will be included in this study. All patients will be followed up for 12-month. The statisticians and rheumatologists who assessed DAS28-CRP are blinded. Investigators and participants are not blind to group assignment. Participants will be randomly assigned at a 1:1 ratio (block size of four) to a smart system of disease management (SSDM) group or a conventional care control group. Upon the completion of 6-month parallel comparison, patients in the conventional care control group will be instructed to use the SSDM app for an extension of 6 months. The primary outcome is the rate of patients with DAS28-CRP  $\leq 3.2$  at month 6.

### 6.2 Clinical Study Site and Data Management

The study does not involve sample collection, storage sites and laboratory research sites.

The data in this study are divided into electronic data and paper data. The paper data should be archived and stored in the order of labeling for inspection. Electronic data files include databases, inspection procedures, analysis procedures, analysis results, code books and instruction documents, etc., which should be stored in categories. Multiple backups of electronic data should be stored on different disks or recording media to prevent damage. All original data should be kept within the required time limit.

### 6.3 Sample Size Determination

1) The rate of DAS28-CRP  $\leq 3.2$  at month 6 is assumed 44.3% in the control group and 52% in the SSDM group; 2) 2-sided  $\alpha$  at 0.05 and power at 90%; 3) 20% attrition rate. The calculation yields a total of 2200 patients. And 2204 is the minimum sample size created by the Random Number Generator.

### 6.4 Populations

(1) Intent-to-treat (ITT) population

The ITT population will include all randomized subjects. Patients will be analyzed according to the study arm to which they were randomized.

#### (2) Modified intent-to-treat (mITT) population

All participants who meet the inclusion criteria, do not meet the exclusion criteria and are randomized.

#### (3) Per-Protocol (PP) population

Patients who complete the treatment and follow-up and outcome information is available at each time point will be included in the PP population. The per protocol analysis includes only adherent participants (adherence rate > 50%). The number of patients in the PP analysis at month 6 was 968 in SSDM group and 886 in control group. The number of patients in the PP analysis at month 12 was 949 in SSDM group and 860 in control group.

Logistic regression, adjusting for baseline stratifications will be used to analyze the binary efficacy variables. The primary and second endpoints will be performed on both the mITT population and the PP population. The primary endpoint will also be analyzed using the worst-case scenario imputation, and the inverse probability of censoring weighted (IPCW) method.

### 6.5 Efficacy Analysis

All efficacy analyses will be performed on both the mITT population and the PP population.

#### 6.6 Primary endpoint analysis

The primary outcome is the rate of patients achieving DAS28-CRP (CRP)  $\leq 3.2$  at month 6. The categorical variables are described by frequency or percentage. We will report the differences between the two groups and associated 95% confidence intervals (CIs) using the Cochran-Mantel-Haenszel with adjustment for central effects. A nominal significance level of 0.05 (two-sided) will be applied to all the analyses. The statistical analyses and reporting will follow the CONSORT guidelines.

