#### 185 1) Randomization

186 Following the evaluation by rheumatologists, eligible participants will be randomized at a 1:1 ratio to a  
187 SSDM group vs a conventional care control group. The randomization sequence was generated with an  
188 interactive web response system (BioVoicer Technology Co. Ltd, Beijing, China) using a block design  
189 (block sizes of 4). The randomization was stratified based on the DAS28-CRP score at the baseline ( $\leq$   
190 3.2, 3.2 - 5.1, or  $> 5.1$ ). Concealment was conducted centrally using an interactive web response  
191 system.

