### 3.6 Statistical analysis

All endpoints will be analyzed in a modified intent-to-treat (ITT) population that excluded patients with incorrect diagnosis (autoimmune diseases other than RA) upon enrolment. Sensitivity analysis will be performed to assess the robustness of the primary analysis using multiple imputation, last observation carried forward imputation, and the worst case scenario imputation. The primary endpoint will also be analysed using the per-protocol (PP) analysis, inverse probability of censoring weighted (IPCW) method. Continuous variables are defined as mean (standard deviation, SD) or median (inter-quartile range, IQR) and will be compared between the two groups using the Student's t-test or Wilcoxon

rank-sum test. Categorical variables are defined as frequency or percentage and compared between the two groups using  $\chi^2$  or Wilcoxon rank sum test, as appropriate. The trend of changes in DAS28-CRP and EULAR responses was calculated from baseline to month 6. Preplanned subgroup analyses will be conducted based on disease activity at baseline. Other subgroup analyses were post hoc. Statistical significance are set at 2-sided  $P < .05$ . All data analyses are conducted using the using the SAS and R.

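### SAP 6.6 adjusts the primary risk difference for centre but omits the DAS28-CRP randomisation strata, so the confidence interval is conservative and the plan's analysis sections disagree

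*Combined protocol and SAP*

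**What the plan says.** - **Randomisation (Protocol 3.3 (2) 1)).** "The randomization was stratified based on the DAS28-CRP score at the baseline", with levels ≤ 3.2, 3.2–5.1 and > 5.1, in blocks of 4, allocation 1:1. Centre is not named as a stratum.
- **Primary endpoint (SAP 6.6).** The difference between groups and its 95% CI are obtained "using the Cochran-Mantel-Haenszel with adjustment for central effects". The same section adds: "A nominal significance level of 0.05 (two-sided) will be applied to all the analyses".
- **Categorical secondary endpoints (SAP 6.7).** The same centre-adjusted method; again no DAS28-CRP strata.
- **Binary efficacy variables (SAP 6.4, under the per-protocol population).** "Logistic regression, adjusting for baseline stratifications will be used to analyze the binary efficacy variables". The text then turns to the primary and secondary endpoints in the mITT and per-protocol sets.
- **Categorical variables in general (Protocol 3.6).** "Categorical variables are defined as frequency or percentage and compared between the two groups using" chi-square or Wilcoxon tests, without adjustment.
- **Baseline DAS28-CRP elsewhere (SAP 6.10).** It defines the planned subgroups.

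No section says how the three methods rank, or that any of them is supportive.

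**The concern.** Blocking within strata balances the arms on baseline disease activity and so lowers the true sampling variance of the risk difference. An analysis that leaves the strata out has the benefit in its estimate but does not report it: its standard error still contains the between-stratum variation that the design has removed. The interval then over-covers and the 5% test runs below 5%. A baseline stratum built from the same score as the endpoint is a natural candidate for a strong predictor, so the loss could matter.

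The second issue is consistency. SAP 6.6 reports a risk difference adjusted for centre; SAP 6.4 implies an odds ratio conditional on the strata. Both apply to the primary endpoint, and a reader cannot tell from the text what role the logistic model has.

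**Working it through.** **Inputs.** From SAP 6.3: month-6 rates of "44.3% in the control group and 52% in the SSDM group", two-sided α 0.05, power 90%, "20% attrition rate". From SAP 6.1: 22 centres. From the earlier SSDM cohort in Protocol 3.4: 491/1,232 = 40% in REM/LDA at baseline; month-6 rates 369/491 = 75.2% for these and 424/741 = 57.2% for the rest, a gradient of about 18 points.

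**1. The plan's sample size.** With unpooled variance,
n per arm = (1.960 + 1.282)² × (0.443×0.557 + 0.52×0.48) / 0.077² = 10.507 × 0.49635 / 0.005929 ≈ 880.
Then 1,760 / 0.8 = 2,200, the stated total. The formula assumes no gain from stratification.

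**2. Half-width without the strata, 880 evaluable per arm.**
1.96 × √(0.49635/880) = 1.96 × 0.02375 = 4.65 points.

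**3. Half-width with the strata.** Remove the between-stratum variance from each arm. For two baseline groups with share w and gradient d it is w(1−w)d². With w = 0.40 and d = 0.18: 0.24 × 0.0324 = 0.00778 per arm.
1.96 × √((0.49635 − 0.01555)/880) = 1.96 × 0.02337 = 4.58 points.
Ratio 4.655/4.581 = 1.016.

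**4. Operating characteristics.** The strata-free test uses a critical difference of 4.655 points, while the true SE is 2.337 points.
- Type I error: 2 × (1 − Φ(4.655/2.337)) = 2 × (1 − Φ(1.991)) = 4.6%.
- Power, strata-free: Φ((7.7 − 4.655)/2.337) = Φ(1.303) = 90.4%.
- Power, stratified: Φ(7.7/2.337 − 1.96) = Φ(1.334) = 90.9%.

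**5. Range.** All rows except the 18-point one are assumptions. The three-level rows also assume a 40/40/20 mix of strata.

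| Control-arm pattern | Half-width, no strata → strata | CI too wide by | Type I error, no strata | Power, no strata → strata |
|---|---|---|---|---|
| 10-point gradient | 4.65 → 4.63 | 0.5% | 4.9% | 90.1% → 90.3% |
| 18-point (Protocol 3.4) | 4.65 → 4.58 | 1.6% | 4.6% | 90.4% → 90.9% |
| 30-point | 4.65 → 4.45 | 4.7% | 4.0% | 91.0% → 92.4% |
| 50-point | 4.65 → 4.05 | 15% | 2.4% | 93.0% → 96.1% |
| Three strata, 61/37/24% | 4.65 → 4.45 | 5% | 4.0% | 91.0% → 92.4% |
| Three strata, 75/30/10% | 4.65 → 3.95 | 18% | 2.1% | 93.5% → 96.9% |

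**6. Simulation check.** 3,000 trials per scenario, 1,760 patients, 22 centres, blocks of 4 within three strata, Mantel-Haenszel difference with Sato variance, effect 7.7 points.
- 18-point gradient: mean half-width 4.66 (centre only), 4.58 (DAS28-CRP strata), 4.64 (66 centre-by-stratum cells); power 90.1%, 90.9% and 89.9%.
- Assumed control rates of 68/33/18%: half-width 4.66, 4.25 and 4.30; power 91.9%, 94.5% and 94.1%.
- The centre-only and strata-only tests disagreed in 2.2% and 2.7% of these trials.
- Under no effect, centre-only and strata-only rejected in 5.2% and 5.7% of trials with the 18-point gradient, and in 3.3% and 4.9% with the steeper rates. Monte Carlo error is about 0.4 points, so the simulation cannot resolve the 4.6% against 5% of step 4, but it does show the conservatism under the steeper pattern.

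Neither calculation models dropout that differs by stratum.

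**The case against.** Several points for the plan stand. Only one method appears under the primary endpoint heading, so a reader who infers three designated primary tests goes beyond the text: the logistic model and the chi-square test are general statements that happen to cover the endpoint. Nor does the SAP ignore the strata throughout, since the logistic model in SAP 6.4 adjusts for its baseline stratifications. Adjusting for centre in a 22-hospital trial is defensible.

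A reader might also infer that planned power is lost. It is not: the 90% was computed without any gain from the strata, and the strata-free analysis reaches at least that in every row above. What goes unused is a bonus.

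A third tempting reading is that the primary test was chosen after the data were seen. SAP 6.4 does contain realised per-protocol counts to month 12, so that sentence was written late. But this does not date the choice of method, and SAP 6.1 states that the statisticians are blinded. The scope is also small: rejecting if any of the unadjusted, centre-adjusted or stratum-adjusted tests was significant occurred in 6.2% of null trials with the 18-point gradient, against 5.2% for the centre-adjusted test alone (the logistic model was not in that set).

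Finally, a 15% excess width cannot be presented as the expected figure. One route to it carries the cohort's 75% maintenance into the control arm and solves for the rest, (0.443 − 0.40 × 0.75)/0.60 = 24%, while setting aside the same cohort's 57%. That mixes two sources.

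Against the plan, the omission in SAP 6.6 and 6.7 and the lack of a ranking remain.

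**Conclusion.** The concern holds as a point of efficiency and clarity. The primary and categorical secondary differences are adjusted for a factor not named in the randomisation and not for the one that is, and SAP 6.4, SAP 6.6 and Protocol 3.6 are not reconciled.

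The direction is conservative whenever baseline DAS28-CRP predicts the outcome. The size depends on how strongly it does. On the documents' own gradient the interval is about 2% too wide, less than 0.1 point of half-width. The 15–18% end needs control-arm gradients that the documents do not report. The 18-point figure is itself uncertain: it comes from SSDM users without a control arm, 64% of whom were at target at month 6 against the planned 44.3% and 52%. It also pools moderate and high activity; splitting them could only raise the explained variance within that cohort.

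The omission causes no bias and no inflated type I error, and the sample size needs no change. Rating: free improvement, should fix.

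**What to change.** 1. In SAP 6.6, make the primary analysis the Mantel-Haenszel risk difference with 95% CI, stratified by the three randomisation strata (≤ 3.2, > 3.2–5.1, > 5.1) as recorded at randomisation. State that the risk difference is the primary effect measure.
2. In SAP 6.7, use the same method for the categorical secondary endpoints.
3. Label the centre-adjusted CMH and the logistic model of SAP 6.4 as supportive, and say which variables its baseline stratifications are.
4. Align the chi-square wording in Protocol 3.6.
5. Do not cross the strata with 22 centres. The 66 cells (1,760/66 ≈ 27 evaluable patients each) give back about three quarters of the half-width gain under the 18-point gradient, (4.64 − 4.58)/(4.66 − 4.58), and all of the simulated power gain (89.9% against 90.1% for centre only).
6. Date the change relative to unblinding. If the primary results are already known, report the stratified analysis as an addition.

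The cost is a few sentences in the SAP and protocol. The strata are already recorded for every randomised patient.
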